## Abstract

**Background:**

Evidence has shown that teleneuropsychology is a crucial tool in the assessment and treatment of individuals with limited access to in-person health services. Nevertheless, studies in Latin America are scarce, and there is a pressing need for studies that test the feasibility of teleneuropsychology and contribute to the development and validation of tools and models, as well as the establishment of normative data for the diverse populations of the region.

**Objective:**

This study aims to conduct the first pilot study in Central America to assess the feasibility of a teleneuropsychology protocol and to generate normative data for a Panamanian sample.

**Methods:**

This is a cross-sectional, descriptive, community-based study derived from the Development and Validation of Teleneuropsychology Normative Data for Older Adults in Florida (FLOAT) study. The study’s final sample will include 150 participants (aged ≥50 years). Participants will undergo initial screening to determine their eligibility and will be included if they have a basic understanding of and access to technological devices such as telephones, tablets, or computers; are free of cognitive impairment or serious health conditions; and provide informed consent. Participants will complete 2 questionnaires to determine if they can continue in the study. Participants who are eligible will be assessed with a teleneuropsychology cognitive battery and will answer questionnaires via a REDCap (Research Electronic Data Capture) link.

**Results:**

Feasibility will be assessed based on an analysis of the tools, funding, expertise, and resources needed to conduct neuropsychological assessments. So far, the study has proven feasible as researchers have been able to obtain a REDCap license and all other material necessary to carry out assessments. As of November 11, 2024, a total of 67 participants aged ≥50 (mean 62.2, SD 7.6) years had been assessed with questionnaires and a complete cognitive test battery. Sociodemographic and clinical characteristics show that participants on average had 16.7 (SD 1.9) years of formal education. A satisfaction questionnaire revealed that most participants were satisfied (22/67, 33%) or very satisfied (39/67, 58%) with the teleneuropsychological assessment, and most participants (58/67, 86%) would recommend this study to others. We expect to assess a similar number of women and men as well as different age groups with the teleneuropsychology battery. We plan to generate normative data for Panamanian adults aged >50 years.

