### Expected Outcomes for Assessing Feasibility

Feasibility will be assessed based on an analysis of the tools, funding, expertise, and resources needed to conduct neuropsychological assessments. Likewise, the Teleneuropsychological Assessment Satisfaction Scale will assess feasibility through the satisfaction of the sample with the teleneuropsychology assessment. The Teleneuropsychological Assessment Satisfaction Scale provides participants with an opportunity to give feedback on various aspects of the assessment, including satisfaction, the use of Zoom and REDCap, instructions, advantages, difficulties, recommendations, and overall time.

So far, the Teleneuropsychological Assessment Satisfaction Scale (Multimedia Appendix 1) has shown that most participants (39/67, 58%) were very satisfied with the teleneuropsychological assessment, while high levels of satisfaction were found with other elements of the assessment, such as the use of the Zoom platform (47/67, 70%), the evaluator (57/67, 85%), or the REDCap platform (33/67, 49%). All participants reported instructions were clear. Most participants (49/67, 73%) were satisfied with being able to do the evaluation from home. Two-thirds of participants (44/67, 66%) reported that they were able to use electronic equipment, such as computers, phones, or tablets. Most participants (37/67, 55%) would recommend a teleneuropsychological assessment to others.

Although most of the sample (53/67, 79%) reported no difficulties at all, main limitations that were stated by participants were internet connection (8/67, 12%), space in which the assessment took place (8/67, 12%), and electronic equipment used (5/67, 7%). Other barriers (12/67, 18%) included the long duration of the assessment, confusing wording in questionnaires, problems with sound, interruptions, difficulties with the assessment materials, problems with the Zoom platform, availability for the assessment, lack of light, and complaints regarding their own abilities.

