## Discussion

### Principal Findings

This paper describes the protocol of a pilot study designed to assess the feasibility of conducting teleneuropsychological cognitive assessments in adults aged ≥50 years. Teleneuropsychology is a technology-based practice that includes collecting patient data using multiple assessment modalities. So far, we have successfully assessed 67 participants with a complete teleneuropsychology evaluation. Our results indicate that our sample is comparable to those in other studies in terms of age [34,38], education level [80,81], and the distribution of men and women [40], characteristics that might contribute to the validity of our design in future analyses.

Moreover, feasibility could also be demonstrated through the successful use of various technological platforms in the assessments, including REDCap and Zoom. This approach to teleneuropsychological assessments has been recommended in other studies [5] and aligns with guidelines established before and during the COVID-19 pandemic [1,7]. To date, very few studies in Panama have used REDCap to capture and store clinical data; nevertheless, this is the first time it is used for neuropsychological assessments, making this an unprecedented study. REDCap has been widely used and recommended for teleneuropsychology studies across various regions worldwide [3,82], as data can only be accessed with a password and server administrator permissions, making the platform ideal for securely storing the collected information [83]. REDCap stands as a viable platform that could be part of the regular clinical practice, ensuring the security, conservation, and confidentiality of gathered data. Likewise, using Zoom as the platform for the assessment is a notable strength, as it has been effectively used in other similar studies [48,84].

In addition, current participant satisfaction has been assessed, revealing that most respondents (39/67, 58%) were highly satisfied with the remote assessment. This aligns with findings from previous studies on participant satisfaction [35,36,42,85]. Key positive aspects highlighted by participants included the use of electronic equipment, the convenience of conducting assessments from home, and the quality of interaction and communication with evaluators. These findings reinforce the strengths of teleneuropsychology identified in another research [41].

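### Feasibility, the first-named aim, is declared from resources obtained and reported only on people with a complete battery; completion among eligible consenting participants should be the outcome

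*Protocol article*

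**What the plan says.** The Objective in the abstract is "to assess the feasibility of a teleneuropsychology protocol and to generate normative data for a Panamanian sample", so feasibility comes first.

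The basis for judging it is given in three places:
- The abstract's Results and the section Expected Outcomes for Assessing Feasibility both say: "Feasibility will be assessed based on an analysis of the tools, funding, expertise, and resources needed to conduct neuropsychological assessments".
- The latter section then adds a participant component: "Likewise, the Teleneuropsychological Assessment Satisfaction Scale will assess feasibility through the satisfaction of the sample with the teleneuropsychology assessment". Table 1 lists that scale under the heading Feasibility.
- Principal Findings adds that successful use of REDCap and Zoom could also demonstrate feasibility.

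The interim verdict in the abstract, introduced by the words so far, is that "the study has proven feasible as researchers have been able to obtain a REDCap license and all other material necessary to carry out assessments".

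The participant-level results all use 67 as denominator. The abstract describes this group as follows: "a total of 67 participants aged ≥50 (mean 62.2, SD 7.6) years had been assessed with questionnaires and a complete cognitive test battery". Principal Findings agrees: "we have successfully assessed 67 participants with a complete teleneuropsychology evaluation". The Participants section gives the same 67 as the number recruited out of a target of 150, and refers to Figure 1 for the numbers invited, recruited and assessed.

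Two would-recommend figures are printed. In the abstract, "most participants (58/67, 86%) would recommend this study to others"; in the feasibility section, "Most participants (37/67, 55%) would recommend a teleneuropsychological assessment to others".

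**The concern.** A pilot of remote testing has to show what share of eligible older adults who agree to take part can finish the battery with usable results. Nothing in the stated basis for feasibility measures that. Licence, tools, funding and expertise are conditions for starting, and they were in hand whether or not participants could finish. Platform use and satisfaction come closer, but they are reported only for people already assessed in full. Someone who consented and was eligible but could not connect, stopped part-way or never started does not appear in any of these figures.

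As the plan stands, its evidence would support calling the method feasible whatever the completion rate was. The abstract's Conclusions already call the approach viable and look ahead to replacing in-person evaluation, so the claim will be relied on.

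**Working it through.** **1. The plan's own figures.** Each is x/67, with an exact (Clopper-Pearson) 95% interval where one is useful.
- Very satisfied: 39/67 = 58.2% (printed 58%).
- Satisfied: 22/67 = 32.8% (printed 33%).
- Together: (39 + 22)/67 = 61/67 = 91.0% (95% CI 81.5 to 96.6).
- Would recommend, abstract: 58/67 = 86.57% (95% CI 76.0 to 93.7). Printed as 86%; it rounds to 87%, which is trivial.
- Would recommend, feasibility section: 37/67 = 55.2% (95% CI 42.6 to 67.4). Printed as 55%.

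**2. What each stated component can tell us.**

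| Component | Where stated | Who it is observed on | Informs completion? |
|---|---|---|---|
| Tools, funding, expertise, resources | Abstract; Expected Outcomes for Assessing Feasibility | The research team | No |
| Use of REDCap and Zoom | Principal Findings | People assessed | Only for those assessed |
| Satisfaction and reported difficulties | Expected Outcomes for Assessing Feasibility | 67 people with a complete battery | No |

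The abstract's verdict rests on the first row alone.

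**3. The denominator.** Let N be the number who consented and passed screening. Completion is 67/N, whereas satisfaction is reported as 61/67, which does not contain N. The text does not give N. Purely as an assumption, to show that the reported figure does not respond:
- N = 67: completion 100%; satisfaction reported as 91.0%.
- N = 80: completion 67/80 = 83.8%; satisfaction reported as 91.0%.
- N = 100: completion 67/100 = 67.0%; satisfaction reported as 91.0%.

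Nothing in the text says that N exceeds 67.

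**4. The final analysis.** Statistical Analyses removes incomplete cases by listwise deletion and makes no exception for feasibility. Ethical Considerations says that what was collected before a withdrawal stays in the analysis. A person who withdraws part-way through the battery is kept under the second statement and dropped under the first. If listwise deletion governs, non-completers stay out of the feasibility figures at 150 as well.

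**5. Why the people left out may matter.** Even among the 67, 8/67 (12%) named the internet connection as a difficulty and 5/67 (7%) the equipment, and 44/67 (66%) reported being able to use electronic equipment. Anyone stopped altogether by such problems would not be in the 67.

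**6. The two recommendation figures.** 58 − 37 = 21 people; 21/67 = 31.3 percentage points on the same denominator. The text does not say how they relate.

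**The case against.** Four points can fairly be made for the authors.

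- **Feasibility does not rest on inputs alone.** A reader of the abstract might infer that it does and that the test therefore cannot fail. The body does not support that: it adds the satisfaction scale, platform use and a tally of participant-reported difficulties (none for 53/67). This stands. The narrower point remains, because none of these measures completion and the abstract's verdict cites only the licence and materials.
- **The verdict is interim.** The sentence opens with so far, and Principal Findings is more guarded. This also stands, but the qualifier changes the timing of the claim and not the reasoning behind it.
- **No attrition is shown.** The same 67 are given as recruited and as fully assessed, and Figure 1, which is not visible here, is said to carry the flow counts. A reader might infer that the satisfaction rate is inflated by drop-out. The documents do not support that inference, and no adjusted rate should be quoted. The fault is that the text does not use the flow counts for feasibility; they may well be reported.
- **Detail may sit elsewhere.** A journal article can leave thresholds and intervals to a fuller plan, so the lack of a pass mark is not held against it. This article does, however, have a section on how feasibility is assessed and does issue a verdict, and both can be judged as written.

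On the recommendation figures, one refers to the study and the other to a teleneuropsychological assessment. They could be two items, or different response categories of one item, on a scale in an appendix that is not shown. Reading them as a contradiction goes further than the text allows.

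**Conclusion.** The point holds in this form: the stated basis for feasibility (resources, platform use, satisfaction) does not measure whether eligible older adults can complete the remote battery. The interim claim in the abstract rests on the licence and materials, which cannot show it. Participant-level results are confined to 67 people described as complete, and listwise deletion would continue that restriction unless feasibility is exempted.

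No bias can be sized. The 91.0% is correct for the 67, and whether it differs among all eligible consenters depends on counts that the text does not give. The conclusion rests on reading the 67 as completers, which two sections say directly.

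The gap between the would-recommend figures, 21 people or 31.3 points, is unreconciled but not a proven error. The change is worth making before the final analysis, and there is time for it with 67 of 150 assessed.

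**What to change.** 1. Make the feasibility outcome the proportion of all eligible consenting participants who complete the battery, with a 95% CI, from the counts already kept for Figure 1. Because consent is taken before the TICS-M and health-history screen, define the denominator as those who consented and then passed that screen.
2. Add two supporting measures: the proportion of scorable results for each test, and the proportion of sessions with a technical failure.
3. Report satisfaction separately, with the number who answered as its denominator.
4. Exempt feasibility from listwise deletion, and reconcile that rule with the statement on keeping data from people who withdraw.
5. In the abstract, replace the claim that feasibility is proven with two facts: the licence and materials are in place, and the completion result to date.
6. State which item or response category 58/67 and 37/67 each refer to, or correct whichever is wrong. Print 58/67 as 87%.

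The cost is wording plus a tabulation of flow counts already held. The technical-failure measure may need a look back through session records if failures were not logged at the time. The downside is that the headline may look less favourable.

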## Methods

### Participants

The protocol of this study is adapted from the Development and Validation of Teleneuropsychology Normative Data for Older Adults in Florida (FLOAT) [63], a study being conducted at the University of Florida with the aim of validating a battery in a healthy sample of older adults with low risk of developing Alzheimer disease and related dementias (ADRD). This study is cross-sectional, descriptive, and community based. As of November 11, 2024, we have recruited 67 (44%) out of 150 participants, all aged ≥50 years and residing in Panama. Details of participants invited to participate, recruited, and assessed are shown in Figure 1.

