## Results

### Preliminary General Characteristics of the Sample

The demographic and clinical characteristics of the sample are summarized in Tables 1 and 2. Participants were mostly female (53/67, 79%) and were on average aged 62.2 (SD 7.6) years. Participants on average had 16.7 (SD 1.9) years of formal education. Most participants have a partner (44/67, 66%). Participants reported few cardiovascular, cerebrovascular, and psychiatric illnesses. Nevertheless, the most common chronic illness is hypertension (22/67, 33%), followed by hypercholesterolemia (19/67, 28%). Most participants identify as White (31/67, 46%) or other (20/67, 30%). Participants showed a high degree of functional independence in performing basic and instrumental activities of daily living. On average, participants had 1.5 (SD 1.8) symptoms of depression.

**Table 1 table1:** Protocol measures for teleneuropsychology assessment.

Measure			Description

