### Limitations

So far, participants reported difficulties primarily related to electronic equipment, internet connectivity, and the environment in which the assessment took place. These limitations are common challenges associated with teleneuropsychology [86,87], and as participants completed the assessment at home, these factors were beyond the assessor’s control. We expect other participants assessed to encounter technological difficulties. The use of REDCap presents both strengths and limitations. On the one hand, this platform ensures secure and confidential storage of test and questionnaire data, as it is only accessible to those connected to the research institution’s server. On the other hand, because the server hosting REDCap is owned by the institution, both the researcher and the participant must have access to the server to use the platform.

Other limitations include the use of convenience sampling for recruitment, which hinders the inclusion of a diverse sample. This resulted in participants with a high level of education and a medium to high socioeconomic level that are not representative of the population. We will actively aim to recruit participants that come from different backgrounds and diverse socioeconomic levels.

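### The expected similar numbers of women and men, and norms by sex and education, do not fit a sample that is 79% women with 16.7 (SD 1.9) years of schooling, and no stated recruitment step addresses sex

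*Protocol article*

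**What the plan says.** All references are to the protocol article.

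- **Target.** Abstract, Methods: "The study’s final sample will include 150 participants (aged ≥50 years". The Participants section reports the state at 11 November 2024: "we have recruited 67 (44%) out of 150 participants".
- **Expectation.** Abstract, Results: "We expect to assess a similar number of women and men as well as different age groups with the teleneuropsychology battery". The same paragraph plans norms for Panamanian adults over 50.
- **Observed sample.** Preliminary General Characteristics of the Sample: "Participants were mostly female (53/67, 79%) and were on average aged 62.2 (SD 7.6) years", and "Participants on average had 16.7 (SD 1.9) years of formal education".
- **Planned use.** Statistical Analyses commits to norms stratified by age (three groups), sex and education level, with z scores formed from the mean and SD of the respective group. Expected Outcomes for Creating Normative Data describes a regression-based adjustment with sex, education and age group as predictors.
- **Recruitment.** Social media, flyers in community centers and newspaper announcements. No step directed at sex is described.
- **Acknowledged limits.** The Limitations section admits that convenience sampling produced a highly educated, unrepresentative sample, and adds: "We will actively aim to recruit participants that come from different backgrounds and diverse socioeconomic levels". It does not mention the sex imbalance. Principal Findings says that "our sample is comparable to those in other studies in terms of age [34,38], education level [80,81], and the distribution of men and women".

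**The concern.** The abstract reports the interim sample and, in the same paragraph, expects similar numbers of women and men. The interim data point clearly the other way, and nothing described in the article is aimed at sex. The one corrective intention concerns background and socioeconomic level.

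This matters because generating norms is a stated objective. A z score based on a group mean and SD is only as good as the number of people in the group. The Dissemination Policy also says that each participant will be rated below average, average or above average against peers of the same age range, sex and education, so a thin cell affects feedback to individuals. For education, a sample concentrated around 16 to 17 years says little about adults with secondary schooling or less, yet the norms are described as being for Panamanian adults in general.

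**Working it through.** **Inputs.** N = 150 (Abstract, Methods); 67 recruited (Participants); 53 women and education mean 16.7, SD 1.9 (Preliminary General Characteristics); three age groups (Statistical Analyses). The article does not state the number of education levels, so 2 and 3 are assumed. It gives no alpha or power for the sex comparison, so two-sided 5% and 80% are assumed.

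**1. The plan's own figure.** 53/67 = 79.1%, as stated. Men: 67 − 53 = 14, or 14/67 = 20.9%. Places left: 150 − 67 = 83.

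**2. What balance would require.**
- 75/75: 75 − 14 = 61 men among 83, or 61/83 = 73.5%.
- 60/40, a loose reading of similar: 60 − 14 = 46 men among 83, or 46/83 = 55.4%.

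**3. What recruitment as described would give.**

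| Share of men among the next 83 | Final men | Final share |
|---|---|---|
| 20.9% (current) | 14 + 83 × 0.209 = 31.3 | 21% |
| 32.6% (upper exact 95% limit) | 14 + 83 × 0.326 = 41.0 | 27% |
| 50% | 14 + 41.5 = 55.5 | 37% |

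The exact 95% interval for the current share of men is 11.9% to 32.6%. Even at its upper limit, the binomial probability of reaching 60 men (46 or more of 83) is about 0.000015.

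**4. Effect on the overall sex comparison.** The detectable standardised difference is approximately (1.96 + 0.84) × √(1/n₁ + 1/n₂). The values below come from the t distribution, which adds slightly to this.
- 31 men and 119 women: d = 0.57.
- 75 and 75: d = 0.46.
- 55 and 95: d = 0.48.

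The loss is modest.

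**5. Effect on stratified norms.** Male cells number 3 age groups × 2 or 3 education levels = 6 or 9. With 31.3 men, the average is 31.3/6 = 5.2 or 31.3/9 = 3.5 per cell. With 5 people, the 95% half-width for a cell mean is 1.96/√5 = 0.88 SD. For a 5th-percentile cut-off under normality it is 1.96 × √(1/5 + 1.645²/10) = 1.34 SD. The whole sample, evenly spread, would average only 150/12 = 12.5 or 150/18 = 8.3 per cell.

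**6. Education.** Twelve years lies (16.7 − 12)/1.9 = 2.47 SD below the mean.
- Under normality: P(≤12) = 0.67%, so 150 × 0.0067 ≈ 1 person.
- Distribution-free upper bound (Cantelli): 1/(1 + 2.47²) = 14%, or at most about 21 of 150 if the mean and SD stay as they are.

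Either count still has to be divided by sex and age.

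**The case against.** Several points on the other side stand.

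- **The sample is not complete.** A reader might infer that the study cannot reach balance. The documents do not support that: 83 places are open and 75/75 is still arithmetically possible. The text says similar, not equal, and sets no 75/75 target. The projection describes unchanged recruitment only.
- **The article is condensed.** The full protocol and the recruitment flowchart are not shown, so it cannot be concluded that no quota exists. What is safe is the mismatch between the stated expectation and the reported data, with no sex-specific step described.
- **Education is disclosed.** The Limitations section admits the skew and gives an aim. The abstract's conclusions say a larger sample is essential for reliable norms, and the study is called a pilot. What remains is that the aim has no stated mechanism and that the promised norms carry no stated education range.
- **Regression does not need filled cells.** This weakens the thin-cell argument wherever the regression method is used. It does not remove extrapolation beyond the observed education range, and the stratified z scores are still planned.
- **The sex comparison is not lost.** A reader might infer that there will be almost no male data. About 31 men still support an overall comparison, as step 4 shows.
- **The comparability statement.** A reader might want it withdrawn. It rests on cited studies that are not at hand, and a mostly female sample may well match them.

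**Conclusion.** The concern holds in a limited form. The expectation of similar numbers does not fit the article's own interim data under recruitment as described: about 31 men of 150 at the current mix, about 41 at the upper 95% limit, and about 37% men even with 50/50 recruitment from now on. The overall comparison of women and men remains usable. The norms are what suffer. Male cells by age and education would average about 5 or 3.5 people, too few for a stable mean and SD, and norms for 12 years of schooling or fewer would rest on very few people.

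The sizes depend on three assumptions: the sex mix continues, there are two or three education levels, and education is roughly normal (without which the share at or below 12 years is bounded only at 14%). The sex imbalance is the main point because it goes unacknowledged; the education skew is secondary because it is disclosed.

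**What to change.** 1. Replace the expectation of similar numbers with the sex mix that recruitment will realistically give.
2. State that the norms apply only to the range of education observed.
3. Where sex-by-age-by-education cells are thin, use the regression-based adjustment already described under Expected Outcomes for Creating Normative Data, not cell means and SDs.
4. Where practical, direct the remaining 83 places towards men and people with less schooling, through targeted advertising or soft targets, at the same N = 150.

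Items 1 to 3 cost only wording and a choice between two methods already in the plan. Item 4 slows recruitment. A hard quota of 61 men and 22 women is not required and would be expensive: at 20.9% men among volunteers, 61 men need about 61/0.209 = 292 eligible volunteers. About 231 of these would be women, so about 231 − 22 = 209 would be turned away. The comparability statement in Principal Findings need not be removed.
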